## 8.2 Adverse events

The definitions of adverse events, device related adverse events and serious adverse events follow the provisions of the International Organization for Standardization (ISO) 14155:

8.2.1 Adverse event (AE) is defined as any medical event that unfortunately happens to patients or clinical Study patients.

8.2.2 Adverse Device Effect (ADE) is defined as an unfortunate event caused by a medical device. This definition includes any event caused by insufficient or inadequate instructions for the use of the device. It also includes any event caused by the human error of the device user.

8.2.3 Serious Adverse Event (SAE) is defined as an adverse event that results in death, life-threatening disease or injury, permanent damage to limb structure or function, need to be hospitalized or extend the existing hospital stay, and need drug or surgical intervention to prevent permanent damage to limb structure or function.

Table 2. potential adverse events and device-related adverse events

| Cardiac events                                                                    | non-cardiac events                                 |
|------------------------------------------------------------------------------------------|-----------------------------------------------------------|
| Myocardial infarction                                                                    | Air embolism                                              |
| coronary artery damage                                                                   | reaction to anesthesia                                    |
| pericardial effusion/pericardial tamponade                                               | cerebrovascular accident/transient ischemic attack        |
| Thromboembolism, including device-related thrombosis                                     | Pseudoaneurysms, arteriovenous fistulas at puncture sites |
| new-onset heart failure or progression of pre-existing heart failure                     | Infection                                                 |
| device embolization                                                                      | localized hematoma/ecchymosis at the puncture site        |
| Inadequate endothelialization of the device surface                                      | vasovagal reaction                                        |
| endocarditis                                                                             | Pneumonia                                                 |
| Hypotensive shock                                                                        | Pneumothorax                                              |
| complete atrioventricular block due to negligence                                        | pulmonary edema                                           |
| vascular wall/vessel damage or insufficiency                                             | Pulmonary embolism                                        |
| Pulmonary stenosis, entrapment or thrombosis                                             | Pleural effusion                                          |
| ventricular arrhythmias requiring defibrillation                                         | phrenic nerve injury                                      |
| Gasification bursts during ablative discharges                                           | Respiratory distress                                      |
| Pacemaker or ICD components damaged                                                      | Skin burns                                                |
| Tachyarrhythmias of atrial origin requiring pharmacologic evaluation and/or intervention | Syncope                                                   |
| Occlusion failed or left atrial appendage occluder other than Watchman was used          |                                                           |

8.2.4 Processes for recording and reporting adverse events

8.2.4.1 The safety monitoring and reporting process should be initiated from the time a patient is enrolled in the study, whether randomized or not.

8.2.4.2 All Serious Adverse Events and all Serious Device-Related Adverse Events should be reported to the study leader immediately upon occurrence.

8.2.4.3 Recording and reporting of non-serious adverse events is limited to cardiovascular and cerebrovascular events. For cardiovascular events, all arrhythmias requiring pharmacologic evaluation and/or intervention should be considered and recorded as adverse events.

8.2.4.4 In case of an adverse event, the information of the adverse event shall be recorded in the hospitalization record and recorded in the case report form (CRF) as soon as possible. The study leader should be notified immediately after completing the CRF form.

8.2.4.4.1 Please refer to the annexes "Data collection" and "Data collection methods".

8.2.4.4.2 Obtain the Electronic Case Report Form (eCRF).

8.2.4.4.3 Selection of adverse event-related visits or unscheduled visits.

8.2.4.4.4 Input the adverse event information into the adverse event notification part of CRF:

- ✓ Date of occurrence of the adverse event.
- ✓ The date the investigator or representative became aware of the adverse event.
- ✓ Complaints/symptoms of adverse events.
- ✓ Initial diagnosis of adverse events.
- ✓ Potential causes of adverse events.
- ✓ Prior medical status associated with an adverse event; the
- ✓ The severity of the adverse event.
- ✓ Correlation of devices in adverse events.
- ✓ The state of adverse events.

8.2.4.4.5 The main investigator or representative joint investigator shall confirm CRF information.

8.2.4.5 Adverse events must be reported to the Ethics Committee (EC).

Note: If an adverse event is documented at the last visit (at 12 months), notification of the adverse event and follow-up information should be submitted to the study director. Planned re-hospitalization due to prior cardiac conditions or other co-morbidities is not considered an adverse event.

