## 3. Study endpoints

### 3.1 Primary endpoints

The primary endpoint was defined as the composite of thromboembolic events such as stroke/transient ischemic attack (TIA), device-related thrombosis (DRT), clinically relevant bleedings, and cardiovascular death or rehospitalization.

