### 3.2 Secondary endpoints

3.2.1 Efficacy of radiofrequency ablation: the success rate of AF- and atrial tachyarrhythmia (ATA, including AF, atrial tachycardia [AT], and atrial flutter [AFL])- freedoms at the one-year and long-term follow-up without the antiarrhythmic drugs after the 3-month blanking period.

3.2.2 Efficacy of LAAO: including the incidence of thromboembolic events (including stroke/TIA) and hemorrhagic events during follow-up, and compared with the risk incidence predicted by CHA2DS2-VASC score and HAS-BLED score.

3.2.3 Procedural-related endpoints of LAAO: including the success rate of occlusion, acute complete occlusion rate, operation time, occlusion time (the time from the presence of the occluder to the release of the occluder), X-ray fluoroscopy time, X-ray fluoroscopy dose, etc.

3.2.4 Procedural-related endpoints of AF ablation: including operation time, pulmonary vein isolation time, first-pass isolation (FPI) rate, X-ray fluoroscopy time, X-ray fluoroscopy dose, etc.

3.2.5 Perioperative safety endpoints: Including complications such as acute thromboembolism, pericardial effusion and pericardial tamponade requiring drainage/surgical intervention, device embolization, vascular-related complications, pulmonary vein stenosis, esophageal injuries, phrenic nerve damage, and coronary artery injury.

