#### 8.9.3.9 Bleeding requiring intervention

- ✓ Bleeding events requiring intervention due to antithrombotic medication during the follow-up period, including bleeding from vital organ sites (e.g., cerebral hemorrhage, gastrointestinal hemorrhage, etc.) and hemorrhage.

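### The recording rules for non-serious events and for bleeding are narrower than the endpoints they feed, so some named endpoint events have no explicit recording route

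*Protocol*

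**What the plan says.** **Endpoints.** Protocol section 3.1 includes in the primary composite "clinically relevant bleedings, and cardiovascular death or rehospitalization". It does not say which bleeds are clinically relevant. Section 3.2.2 takes as a secondary endpoint the "incidence of thromboembolic events (including stroke/TIA) and hemorrhagic events during follow-up", without a limit on severity or cause. The perioperative safety list in section 3.2.5 ends with "pulmonary vein stenosis, esophageal injuries, phrenic nerve damage, and coronary artery injury", and none of these items is restricted to serious cases.

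**Recording.** Section 8.2.4.2 covers serious events of every organ system: "All Serious Adverse Events and all Serious Device-Related Adverse Events should be reported to the study leader immediately upon occurrence". For the rest, section 8.2.4.3 says: "Recording and reporting of non-serious adverse events is limited to cardiovascular and cerebrovascular events". Among the visit data in section 8.9.3, the bleeding item is section 8.9.3.9: "Bleeding events requiring intervention due to antithrombotic medication during the follow-up period". In Table 1 (section 8.1) the adverse-event item at each visit refers back to section 8.2. Appendix C describes the follow-up form as a record of general condition and medication use.

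**The concern.** An endpoint can be analysed only if sites are told to record it. Here the endpoint sections are wide and the recording sections are narrow. A site that follows section 8.2.4.3 to the letter would leave out a nosebleed that needed no treatment, or a transient phrenic nerve palsy that did not prolong the stay. The first is a hemorrhagic event under 3.2.2 and the second is a safety endpoint under 3.2.5.

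The consequence is under-counting of named endpoints. A statistical analysis plan cannot repair it, because an analysis cannot restore events that were never entered. Section 8.9.3.9 also ties collection to antithrombotic medication, so a view on cause comes before the event is recorded. Neither 3.1 nor 3.2.2 has that condition, and a comparison between two randomised arms does not need it.

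**Working it through.** The protocol gives no figure on this point, so the check matches each endpoint component to a recording route.

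| Endpoint component | Where counted | Recording route | Gap |
|---|---|---|---|
| Death | 3.1 | 8.3, all deaths | none |
| Stroke, TIA, thromboembolism | 3.1, 3.2.2 | 8.9.3.8, symptomatic or not | none |
| Device-related thrombus | 3.1 | 8.9.3.7, at TEE follow-up | none |
| Unplanned rehospitalisation | 3.1 | serious event under 8.2.3, reported under 8.2.4.2 | none |
| Serious bleed, any site | 3.1, 3.2.2 | 8.2.4.2 | none |
| Non-serious bleed, needs intervention, due to antithrombotics | 3.1, 3.2.2 | 8.9.3.9 | none |
| Non-serious bleed, no intervention or another cause | 3.2.2; 3.1 depending on definition | none stated, unless cardio- or cerebrovascular | **yes** |
| Pericardial, device, vascular, pulmonary vein and coronary complications | 3.2.5 | 8.2.4.2, or 8.2.4.3 if read as cardiovascular | none on that reading |
| Non-serious phrenic nerve damage | 3.2.5 | none stated | **yes** |
| Non-serious esophageal injury | 3.2.5 | none stated | **yes** |

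Three steps support the rows marked yes.

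1. *Seriousness.* Section 8.2.3 makes an event serious if, among other criteria, there is "need to be hospitalized or extend the existing hospital stay". A bleed or nerve injury that meets none of those criteria is non-serious and falls under 8.2.4.3.
2. *Organ system.* Table 2 in section 8.2 places "phrenic nerve injury" in its non-cardiac column, so its non-serious form is outside 8.2.4.3 on the protocol's own classification. Esophageal injury does not appear in Table 2 and is neither cardiovascular nor cerebrovascular. A nasal, urinary or gastrointestinal bleed is normally outside both classes too.
3. *Other routes.* The adverse-event item in Table 1 leads back to section 8.2 and so to the same limit. Nothing in section 8.9.3 asks for phrenic or esophageal injury, and its bleeding item has the two conditions already described.

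**What equal loss in both arms would cost (illustration only).** The protocol gives no event rate for the composite, so every rate here is an assumption. Take the 71 evaluable patients per arm from section 7, a control event proportion p1, and p2 set so that power is 80% with full capture. Power is Φ{[|p1 − p2| − 1.96·√(2p̄(1−p̄)/71)] / √[(p1(1−p1)+p2(1−p2))/71]}, with p̄ = (p1+p2)/2. If a share s of composite events is recorded in both arms, p1 and p2 become s·p1 and s·p2.

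| p1, p2 | s = 1 | s = 0.9 | s = 0.8 | s = 0.7 |
|---|---|---|---|---|
| 0.20, 0.047 | 80.0% | 75.0% | 69.2% | 62.7% |
| 0.30, 0.111 | 80.0% | 74.5% | 68.2% | 61.2% |
| 0.40, 0.188 | 80.0% | 73.8% | 66.9% | 59.3% |

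This shows only how power responds to missed events. The protocol does not say what share would be missed, and the share could be close to zero.

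**The case against.** The strongest reply is that section 8.9.3.9 stands apart from adverse-event reporting. It has no seriousness or organ-system limit, and it names gastrointestinal hemorrhage. A bleed that leads to a change of medication is naturally read as needing intervention, so many non-serious bleeds are collected after all. If clinically relevant bleeding in 3.1 is meant to be bleeding that needs intervention, the primary endpoint and its collection largely agree. Under section 8.8.8.2 nearly all patients take antithrombotic drugs throughout follow-up, so the condition on cause may remove few events. All of this stands. It narrows the gap but does not close it: 3.2.2 and 3.2.5 are unrestricted as written, and the meaning of the primary component is left to the reader.

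Three stronger readings are tempting and are not supported.

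- *Parts of the primary endpoint are never captured.* The protocol does not show this. The primary component is affected only if the undefined term is wider than 8.9.3.9, or if bleeds from other causes count.
- *The loss would differ between arms*, because a leak of 5 mm or more extends anticoagulation under 8.8.8.2 and the arms are expected to differ in leak. Section 1.3 expects a difference in newly detected leak. The only leak size it gives is no more than 3 mm, from another group's series, which is below the 5 mm trigger. Nothing in the protocol predicts a difference in leaks of 5 mm or more, or in the fraction of bleeds missed.
- *About 3 to 10 patients per arm would be lost.* That is 101 × 0.03 = 3 and 101 × 0.10 = 10. It rests on assumed rates of non-major bleeding and on the loss of every such bleed, although 8.9.3.9 collects those that need intervention. It is a ceiling on the worst reading, not an estimate.

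**Conclusion.** The inconsistency is real but limited. Non-serious bleeds that need no intervention or are not attributed to antithrombotic drugs, non-serious phrenic nerve damage and non-serious esophageal injury have no explicit recording route. For 3.2.2 and 3.2.5 this follows from the text without further assumptions, apart from the ordinary view that such events are neither cardiovascular nor cerebrovascular. For the primary endpoint it depends on a definition that the protocol does not give.

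Neither the number of events lost nor any imbalance between arms can be derived from the protocol. This should be fixed: named endpoints would be under-counted in a way that no later analysis could correct. It is not a demonstrated failure of the primary analysis.

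**What to change.** 1. In section 8.2.4.3, exempt every event named in 3.1, 3.2.2 and 3.2.5 from the limit, whatever its seriousness or organ system, and give these events their own case report form fields. Add esophageal injury to Table 2.
2. Reword section 8.9.3.9 to record all bleeding, with its date and a grade on a standard severity scale, and remove the condition on cause. If attribution is of interest, record it as a separate field after the event is entered.
3. In section 3.1, define clinically relevant bleeding by that grade, so that the endpoint and its collection match. If only bleeding that needs intervention is intended, section 3.1 should say so.

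The cost is wording, a few form fields and slightly more recording by sites at visits already planned. No new visit or test is needed.

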### 8.3 Patient deaths

#### 8.3.1 Process for recording and reporting patient deaths

8.3.1.1 The safety monitoring and reporting process should be initiated as soon as the patient is enrolled in the study, whether randomized or not.

8.3.1.2 All patient deaths should be recorded and reported to the study leader as soon as they occur.

8.3.1.2.1 Please refer to the annexes "Data collection" and "Data collection methods".

8.3.1.2.2 Obtain the Electronic Case Report Form (eCRF).

8.3.1.2.3 Selection of patient death-related visits or unscheduled visits.

8.3.1.2.4 Input the patient death information into the patient death notice part of CRF:

- ✓ Date of death.
- ✓ The date of death is known to the researcher or representative.
- ✓ Record the place of death (e.g., hospital, care center, patient's home).
- ✓ Whether there were witnesses to the death.
- ✓ Whether or not an autopsy was performed.
- ✓ Provisional cause of death.
- ✓ Main causes of death.
- ✓ Details of death.
- ✓ Whether the investigator or representative was aware of the serious adverse event associated with the death.

8.3.1.2.5 Submit CRF. When CRF is submitted, an alarm is generated to notify the person in charge.

8.3.1.2.6 CRF must be authorized by PI or representative joint investigator.

8.3.1.2.7 The death of the patient means the early end of the patient's participation in the study.

Perfect CRF endpoint.

8.3.1.2.8 By national and local laws and regulations, the investigator must notify the ethics committee.

#### **8.4 Early termination of patient participation studies**

Every effort should be made to maintain patient retention in the clinical study until completion of the study. The

8.4.1 The patient himself/herself or his/her family may request to withdraw from the study at any time; he/she may withdraw from the study without acknowledgment and without affecting his/her relationship with the investigator.

8.4.2 In the event of the death of the patient, refer to section 8.3, "Death of the patient";

8.4.3 The investigator may withdraw a patient from the study at any time to optimize the interests of the patient.

8.4.4 The Investigator may evacuate a patient if the patient fails to comply with the scheduled visit and/or study procedures. The patient will be considered "lost"; patient will be considered "lost" when he/she is out of contact on 3 occasions (including at least 3 calls to the patient/emergency contact by the investigator/representative at the recorded telephone number on non-simultaneous days); and the patient will be considered "lost" if he/she initiates contact with the investigator/representative after he/she has been judged "lost" and the date of contact is within the time window of the visit. If the patient is determined to be "lost" and then takes the initiative to contact the investigator/representative, and the date of contact falls within the time window of the visit, the patient will be removed from the "lost" status and continue to be followed up according to the patient's wishes, or the patient will be determined to be withdrawn from the study.

8.4.5 If the patient withdraws and ends the study, CRF termination information should be recorded as soon as possible. The investigator shall be notified after CRF is completed.

8.4.5.1 Please refer to the annexes "Data collection" and "Data collection methods".

8.4.5.2 Obtain the electronic case report form (eCRF);

8.4.5.3 Input the information of patients' early termination of the study into the end of CRF:

- ✓ Date of conclusion of the study.
- ✓ Reasons for ending the study early.

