## 7. Sample size calculations

In this study, 202 AF patients from 14 centers in China who were referred to undergo a combined procedure of LAAO combined with radiofrequency ablation were enrolled. Calculate the formula according to the sample size, with a 1:1 grouping ratio,  $N1=N2=2 [(t_{\alpha/2} + t_{\beta/2}) \delta / \sigma]^2 (\alpha=0.05, 1-\beta=0.8)$  and Study data of intergroup differences in our previous single-center, retrospective study. The sample size required for each group was calculated to be 71 cases, and the minimum sample size required for each group was 89 cases, taking into account a 20% lost rate of follow-up. Taking other factors into consideration, 101 cases were planned to be enrolled in each group.

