| Randomization      | After signing the informed consent form, prior to surgery                   | Not applicable | 
 
Uniform computerized randomization of core laboratories, randomized grouping by serial number of enrollment
 
                                                                                                                                                                                                                                                                                                                                                                                                                                                                                                                                                                                                                                                                        |
| Combined procedure | within 30 days of the baseline visit                                        | Not applicable | 
 
Collect operation related data (anesthesia mode, operation time, X-ray fluoroscopy dose and time, contrast agent dose, etc.)
 
Collection of data related to radiofrequency ablation (including ablation procedure, ablation time, pulmonary vein isolation time, single-loop isolation, patch location, non-pulmonary vein triggered foci, ablation of combined arrhythmias, etc.)
 
Collect LAAO related data (multi position angiography and measurement results, whether to use the "steel ball method" for positioning, intraoperative ultrasonic measurement results, number and size of occluders, times of deployment and recovery, maximum diameter/compression ratio of occluder after release, marginal shunt, and pull test)
 
Adverse events (*)
 
 |

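### Section 8.4.3 lets the investigator end a randomised patient's participation at any time, and nothing keeps that patient in primary-endpoint follow-up, so later events can be lost selectively

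*Protocol*

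**What the plan says.** Protocol section 8.4 gives the investigator two ways to take a patient out. Section 8.4.3 is open-ended: "The investigator may withdraw a patient from the study at any time to optimize the interests of the patient". Section 8.4.4 concerns non-compliance: "The Investigator may evacuate a patient if the patient fails to comply with the scheduled visit and/or study procedures". For the end-of-study part of the CRF, section 8.4.5.3 lists two items: "Date of conclusion of the study" and "Reasons for ending the study early". Section 5.2.7 covers withdrawal by the patient and refers to 8.4 for documentation; it adds no follow-up.

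Two texts lean the other way. Section 8.4 opens with "Every effort should be made to maintain patient retention in the clinical study until completion of the study", and section 8.3.1.2 says "All patient deaths should be recorded and reported to the study leader as soon as they occur". Neither says whether collection goes on after a withdrawal.

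Table 1 in section 8.1 places randomisation "After signing the informed consent form, prior to surgery". The arms differ in the order of two steps within one operation (8.8.1, 8.8.3). The primary endpoint is a clinical composite (3.1), follow-up is twelve months (5.2.4), and the groups are compared by Kaplan-Meier analysis (9).

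**The concern.** As written, 8.4.3 ends study participation, not merely a study procedure. The person who decides can know the arm. Because randomisation precedes surgery, the rule could be applied to a patient whose assigned order the operator dislikes. It could also be applied later, to a patient who is doing badly. A withdrawal made for the patient's benefit is plausibly related to prognosis, and in an open trial its frequency may differ by arm.

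A Kaplan-Meier comparison is valid only if those who leave early have the same later risk as those who stay. If they do not, the primary contrast is distorted, and the direction depends on who leaves and from which arm. Device-related thrombosis is especially exposed: it is a primary component that is looked for by TEE at 45 days, so a patient withdrawn before then may never be examined for it.

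An SAP can say how withdrawals are analysed, but it cannot recover outcomes that the protocol did not collect.

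**Working it through.** **Reading the texts together**

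1. Power to withdraw: 8.4.3, at any time, without criteria or review.
2. Data asked for at termination: date and reason (8.4.5.3).
3. Data captured before termination: serious adverse events, which include hospitalisation (8.2.3, 8.2.4.2); deaths (8.3.1.2); thromboembolism and bleeding needing intervention at visits (8.9.3.8, 8.9.3.9); device-related thrombosis at TEE (8.9.3.7). Appendix C has separate adverse-event, death and unscheduled-visit tables.
4. Data required after termination: none found.

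The gap therefore lies in step 4. Step 3 covers most of the time before withdrawal. One smaller hole remains there: no closing visit is specified, so a non-serious bleed since the last visit could be missed.

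**The plan's own figure**

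Section 7 inflates 71 per arm, "taking into account a 20% lost rate of follow-up", to 89. Check: 71 / (1 − 0.20) = 88.75, rounded up to 89. This reproduces. The 71 cannot be checked, because no effect size or event rate is given. The planned number is 101 per arm.

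**Illustration 1: withdrawn patients have a higher risk**

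Assumed, not in the protocol: the same true 12-month risk p in both arms; k patients with risk q withdrawn from one arm only, before any event, and dropped. Observed risk in that arm = (101p − kq) / (101 − k).

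| p | k | q = 2p | Difference (points) | q = 3p | Difference (points) |
|---|---|---|---|---|---|
| 20% | 5 | (20.2 − 2.0)/96 = 19.0% | 1.0 | (20.2 − 3.0)/96 = 17.9% | 2.1 |
| 20% | 10 | (20.2 − 4.0)/91 = 17.8% | 2.2 | (20.2 − 6.0)/91 = 15.6% | 4.4 |
| 30% | 5 | (30.3 − 3.0)/96 = 28.4% | 1.6 | (30.3 − 4.5)/96 = 26.9% | 3.1 |
| 30% | 10 | (30.3 − 6.0)/91 = 26.7% | 3.3 | (30.3 − 9.0)/91 = 23.4% | 6.6 |

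For scale, the standard error of the difference with 101 per arm is √(2p(1 − p)/101): 5.6 points at 20% and 6.4 points at 30%.

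**Illustration 2: only patients who would have had an event leave**

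This is the extreme case, since it assumes perfect prognosis. A fraction f of would-be event patients in one arm is withdrawn and dropped, so that arm's observed risk is p(1 − f)/(1 − fp). The comparison is a two-sided pooled two-proportion test at 0.05. Example with p = 20% and f = 20%: observed risk 0.16/0.96 = 16.7%, difference 0.0333, standard error 0.0551, ratio 0.605. Type I error = Φ(−1.96 + 0.605) + Φ(−1.96 − 0.605) = 0.088 + 0.005 = 0.093.

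| p | Withdrawn at f = 20% | Type I error, f = 0 | f = 10% | f = 20% |
|---|---|---|---|---|
| 10% | about 2 | 0.050 | 0.056 | 0.074 |
| 15% | about 3 | 0.050 | 0.058 | 0.084 |
| 20% | about 4 | 0.050 | 0.060 | 0.093 |
| 30% | about 6 | 0.050 | 0.063 | 0.107 |

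**The case against.** The strongest reply is that 8.4.3 protects patients and that the harm is hypothetical. Much of this stands.

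- A reader might infer that after the operation only observation is left to stop, so that withdrawal does nothing but discard data. The protocol does not support that. It prescribes antithrombotic and antiarrhythmic treatment, cardioversion rules and TEE after surgery (8.8.8.1 to 8.8.8.3, 8.9.3.7). Leaving the study can change that care, so the clause has a purpose after surgery too.
- A reader might infer from the two-item list in 8.4.5.3 that events before withdrawal are lost. Most go on other forms. The CRF itself is not shown, so the exact content of the termination form is also an inference.
- A reader might state as fact that events are lost selectively. The protocol shows a route, not its frequency or direction. It also urges retention, and 8.4.4 lets patients counted as lost return.
- The 20% in section 7 is a general loss rate used to get from 71 to 89. It is not a quota for investigator withdrawals, and the step from 89 to 101 rests on other, unstated factors.
- Both illustrations put every withdrawal in one arm and drop patients entirely, whereas under Kaplan-Meier they would contribute until they leave. At 20% risk the differences in the first illustration are below one standard error. How withdrawn patients are censored is not stated in section 9 and may be in an SAP not seen here.

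None of this supplies the missing rule. Protecting the patient requires freedom to change treatment; it does not require outcome collection to end.

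**Conclusion.** The point holds as a design weakness that can cause bias, not as a demonstrated loss of events. Section 8.4.3 allows open-ended withdrawal by someone who can know the arm, and no text keeps the patient under observation for the primary endpoint afterwards. That the investigator is unmasked is inferred: no masking is described, and the operator cannot be masked to the order.

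The documents give no basis for the size. Under the assumed risks of 20% and 30%, the first illustration gives false differences of 1.0 to 4.4 and 1.6 to 6.6 points. In the extreme second one, losing 2 to 6 patients from one arm raises the type I error from 0.050 to between 0.074 and 0.107. The direction could be either. Enlarging the sample for losses restores numbers but does not remove this kind of bias. No stated sample size changes.

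**What to change.** 1. Reword 8.4.3: the investigator may stop or change protocol procedures or treatments in the patient's interest, but the patient stays in the assigned group and is followed for primary-endpoint events to 12 months, by visit, telephone or hospital record. Follow-up ends early only if consent to it is withdrawn or the patient cannot be reached.
2. Align 4.4, 4.5, 8.4.4 and the note to 8.5, which links deviations to the termination form. If 8.4.3 alone were changed, the protocol would contradict itself.
3. Add to 8.4.5.3 vital status and, for each primary component, whether it has occurred and when. This checks the existing forms up to termination; only item 1 secures later events.

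The cost is some rewording, a few CRF fields and a few extra telephone contacts, which can fall at existing visit times. One limit remains: telephone and record follow-up will not reveal device-related thrombosis in a patient who declines imaging, so missing TEE should be recorded as such.
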